### Care-as-usual (CAU)

In the control condition, girls receive unchanged CAU including teaching practices they are already exposed to in their current schools. No other classroom-based mindfulness interventions will be implemented during the intervention period of the cRCT.

### Train the trainers to deliver the program

The training sessions will be delivered in academic year 2023/2024 (cohort 1) and 2024/2025 (cohort 2) by mindfulness-trained staff members (i.e., PI, PhD students and external staff members). All HFPM trainers have followed an 8-week Mindfulness for Life course at the Oxford Mindfulness Foundation in academic year 2021/2022 or 2022/2023 (seven 2-h sessions per week and one whole day session, supported by a course booklet and several digital guided mindfulness practices to facilitate mindfulness practice during and after the 8-week course). Furthermore, they will all have an established mindfulness practice of more than 6 months before the prevention program starts.

Between October 2023 and January 2024, all trainers will attend a 4-day training program to learn how to deliver the program to the friendship dyads. To maximize fidelity, all trainers have to reach adequate adherence and competence standards before they start teaching trial dyads. This will be conducted through roleplay. During program implementation, all trainers will receive weekly supervision on competence and adherence by the PI [name], who also finalized the Mindfulness Frame by Frame course (Oxford Mindfulness Foundation) and the Teacher Training course “Dot-b” (MISP). During the cRCT, competence and adherence will be monitored. Following study procedures of the MYRIAD mindfulness trial regarding the use of the MBI: TAC [63, 64], an independent rater ([name]) and PI [name] will weekly randomly select a subset of 10% of the videotapes for fidelity monitoring using the MBI:TAC instrument.

### Measures

#### Screening measure (girls)

Self-reported co-rumination will be measured with a subset of items from the Co-Rumination Questionnaire-Short [21] which is based on the original 27-item Co-Rumination Questionnaire [9]. The Co-Rumination Questionnaire-Short consists of 17 items and measures the extent to which girls typically co-ruminate with their best or good same-gender friend, using a 5-point Likert scale, ranging from 0 (*not at all true*) to 4 (*really true*). The five items that will be used for this screening are “When we talk about a problem that one of us has, we try to figure out every one of the bad things that might happen because of the problem,” “When we talk about a problem that one of us has, we spend a lot of time trying to figure out parts of the problem we can’t understand,” “When we talk about a problem that one of us has, we talk a lot about how bad the person with the problem feels,” “When we talk about a problem that one of us has, we’ll talk about every part of the problem over and over,” and “When we talk about a problem that one of us has, we talk about all of the reasons why the problem might have happened.” The English five-item version showed very good reliability of change (RCI = 0.89; [65]). We also calculated reliability statistics for girls (age 13 and 14) living in the Netherlands. Cronbach’s alpha showed good reliability, with *α* = 0.85 and 0.74 for 13- and 14-year-old girls, respectively (unpublished data, data available from the authors). These data will be collected via Qualtrics.

### Primary outcome variables

All data will be collected via Qualtrics.

#### T0, T1, T2, T3, T4, and 1-year follow-up measures T5 (girls)

##### Self-reported negative affect: co-rumination

The original measure [9] to assess co-rumination included 27 items that measure the extent to which youth typically co-ruminate with same-sex friends. Nine content areas are covered, including (a) frequently discussing problems, (b) discussing problems rather than doing other activities, (c) friend encouraging discussion of problems, (d) target child encouraging friend to discuss problems, (e) discussing repetitively the same problem, (f) speculating about cause of problems, (g) speculating about consequence of problems, (h) trying to understand parts of problems, and (i) focusing on negative affective feelings. The items focus on assessing a more extreme form of discussing problems beyond mere self-disclosure.

For the present study, 9 items (1 for each of the topic areas) will be used to assess co-rumination at T0, T1, T2, T3, T4, and T5 1-year follow-up (Co-rumination Questionnaire-short; CRQ-short). These items include: “We talk about problems that my friend or I are having almost every time we see each other”, “When we see each other, if one of us has a problem, we will talk about the problem even if we had planned to do something else together,” “When my friend has a problem, I always try really hard to keep my friend talking about it.,” “When I have a problem, my friend always tries to get me to tell every detail about what happened,” “When we talk about a problem that one of us has, we’ll talk about every part of the problem over and over.,” “When we talk about a problem that one of us has, we talk about all of the reasons why the problem might have happened.,” “When we talk about a problem that one of us has, we try to figure out every one of the bad things that might happen because of the problem.,” “When we talk about a problem that one of us has, we spend a lot of time trying to figure out parts of the problem that we can’t understand.,” and “When we talk about a problem that one of us has, we talk a lot about how bad the person with the problem feels.”

Rose [9] reported that her 27-item measure was unifactorial, and a factor analysis of the 9 items used in Hankin and colleagues [21] similarly revealed a single factor. Internal consistency in this sample with 9 items was a 0.89 at Time 1, 0.91 at Time 2, and 0.91 at Time 3. Girls will respond to the items using a 5-point Likert scale ranging from 0 (*not at all true*) to 4 (*really true*) and scores will be the mean rating of the nine items. Rose and colleagues (2007) reported excellent internal consistency, good test–retest reliability, and validity [11].

##### Self-reported (early-onset risk for) depressive symptoms/disorder

Self-reported degree of depressive symptoms will be measured with the Child Depression Inventory (CDI-2; [66]), which includes 28 items. All items offer three graded options from 0 to 2, of which one should be chosen (e.g., 0 = “*I am sad once in a while*,” 1 = *I am sad many times*,” and 2 = “*I am sad all the time*”) with higher scores indicating more depressive symptoms. Total scores could range from 0 to 56, and a score of 12 or above is considered a clinically relevant score [66]. The CDI-2 has good internal consistency, test–retest reliability, and convergent validity [66].

#### T0 and T4 measures (girls)

##### Observed regulation of negative affect: co-rumination

Co-rumination and the topic of problems (interpersonal problems/non-interpersonal problems) will be observed with the Dutch version of the standardized Problem Talk Task (PTT; [22, 67]. Participation of girls will take place online using the protected Teams-environment of Rotterdam University of Applied Sciences. Both girls will receive links to the Teams-observations via email. The observations will be recorded via Teams. The PTT will start with a short warm-up task. Girls will be asked to plan a party together and to discuss the guest lists, the location, the theme of the party, etc. After the warm-up task, dyads will be told that they will have 16 min to discuss problems or worries they want to share and that are allowed to discuss anything about the problems and/or worries. They will be asked to discuss each friend’s problem and will be told that they are allowed to spend as much time as they want to on each person’s problem/worries. They will be told that, if they finish talking about problems, they could talk about something else.

##### Coding process

All video recordings will be stored and coded in Research Cloud. There will be three major aims of coding. The first is to provide information regarding the degree to which the girls participated in problem talk. The second aim is to provide information regarding how girls responded to friends’ statements about problems and/or worries. The third aim is to provide information about the topics on which girls co-ruminate. A team of two coders (both PhD students) will code the data. The coders will first obtain interrater reliability based on 25% of the interactions and then individually code the remaining interactions.

To determine how often girls participate in problem talk, all thought units that the girls produced will be coded as Own-Problem Statements, Friend-Problem Statements, or Non-Problem Statements. To do this, interactions in the PTT will be first transcribed by students of Developmental Psychology of VU Amsterdam and then segmented by the PhD students into thought units, or logical divisions of speech identified based on contextual and syntactic clues, such as pauses, changes in ideas, or changes in who was speaking [68, 69]. Coders will first classify all thought units according to whether they are Own-Problem Statements (i.e., statements about the speaker’s own problems) or not. Next, the thought units will be classified according to whether they are Friend-Problem Statements (i.e., statements about the speaker’s friend’s problems) or not. Each girl will be given a score for the total number of Own-Problem Statements, Friend-Problem Statements, and Non-Problem Statements that they produce.

Adolescents’ responses to friends’ Own-Problem Statements will be coded next. All turns with at least one Own-Problem Statement will be identified. A turn is defined as a stream of uninterrupted speech with one or more thought units. A turn begins when a girl begins to speak. A turn ends when the friend speaks or there is a pause of approximately 15 s. Like prior coding approaches [68], each thought unit produced by the adolescent in the turns directly following turns produced by the friend that included at least one Own-Problem Statement will be coded into one of the 10 response categories. Six of the categories are considered Positive Engaged responses: Support/Agree (e.g., “I think you did the right thing.”), Question (e.g., “When did it happen?”), Related Experience (statement on problem topic about one’s own experience that is related to the statement from the original speaker, e.g., “I feel sad when she doesn’t return my calls too.”), Information/ Opinion (new information about problem, e.g., “And her parents let her stay out past midnight” or an opinion presented in a relatively neutral manner, e.g., “I thought he worked hard on that.”), Acknowledge/Prompt (conveys the listener is paying attention, with or without explicitly encouraging the speaker to continue, e.g., “Uh-huh,” “Oh,” “Keep talking.”), Advice Giving (e.g., “You should call her.”).

Three of the responses are Negative: Changing the Subject (statements that are not focused on the problem topic, e.g., “I’m hungry” or that focus on the adolescent’s experience with the problem topic in a manner that draws attention away from original speaker, e.g., “Well, the person who she ignores the most is me!”), Minimization/Non-Support (explicitly non-supportive statements or statements that convey the problem is less important than the speaker portrayed it to be, e.g., “Everyone hates it when you say that,” “That’s not a problem.”), and Silence/No response (no response and a break in the conversation for about 15 s or more). The final response is Humor (conveys humor, joking, or non-hostile sarcasm). There is an Other category for thought units that were unintelligible or had no substantive meaning (e.g., “Well,” “Um”); the Other category will be not used in analyses.

Summed scores will be computed for each girl that are the total number of responses of each type that the adolescent produce. The decision to use summed scores for the analyses (as opposed to proportion scores, i.e., the percent of responses of each type out of the total number of responses) is based on the idea that the total number of experiences that adolescents have in which they hear positive engaged, negative or humorous response statements (in other words, the cumulative experience of hearing these responses) should have a particular critical influence on friendships.

Finally, all the problem-focused thought units will then be assigned one of the topic codes. The topic codes were generated a priori based on the literature reviewed regarding challenges during adolescence. Three topic codes are interpersonal: family, peers (nonromantic), and romantic interests. Three are not interpersonal: academics, athletics and other extra-curricular activities, and jobs and money. Finally, each problem-focused thought unit will be timed. The number of seconds that friend dyads spent on each problem topic will be summed. For each step, 25% of the dyads will be double coded. Interrater reliability will be computed separately for T0 and T4.

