#### Concealment mechanism

Intervention allocation will be concealed by using a web-based application with a computer-generated list that will not be disclosed. Participants and researchers are aware of allocation.

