### Assignment of intervention: blinding

#### Who will be blinded

Due to the organizational structure of the prevention program, students, parents, school, and research staff will not be blind to treatment allocation.

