## Discussion

The proposed study aims to provide insight into the short-term (T1, T2, T3 and T4) and long-term effects (T5) of the HFPM secondary school-edition prevention program on girls’ co-rumination, internalizing problems, wellbeing, and social-emotional behavioral functioning.

The HFPM program is school-based mindfulness and psychoeducation blended prevention program aimed at girls aged 13–15 years within secondary schools. This program was developed between 2020 and 2023 using the Intervention Mapping Approach for planning health promotion programs. The program comprises of 14 guided, weekly online lessons with mindfulness practices and psychoeducation, guiding the dyadic use of the application App yourself Happy. The goal of this program is to train 160 Dutch (80 dyads) high-risk girls between ages 13 and 15 to shift dyadic maladaptive ER patterns to more adaptive ER strategies within their dyadic interactions, while continuing to reap the benefits of their close, intimate friendships and exploring healthy, new alternatives for excessive co-rumination.

The objective of the HFPM cRCT is to evaluate the effectiveness of the prevention program HFPM, delivered by experienced mindfulness health professionals, compared with CAU and to unveil mechanisms of change. Self-reported risk for (early onset) depression and anxiety and self-reported and observed co-rumination will be the primary outcomes. Secondary outcomes will be self- and friend-reported friendship quality, self-reported positive and negative affect, self-reported interpersonal reactivity to personal distress, self-reported interpersonal responses to positive affect, self-reported anhedonic symptoms, self-reported mastery, and parent-reported health care use.

If the trial demonstrates that this prevention program is effective, secondary schools will be able to prevent excessive co-rumination in young adolescent girls and to improve girls’ short- and long-term mental health outcomes and friendship quality. The trial will also contribute to our understanding for whom, and under which circumstances, the prevention program is most effective, so schools will be able to match the intervention working mechanisms with the specific needs of subgroups of girls within schools. This knowledge will result in continuous improvements in the development of the train-the-trainer program, including training and supervision of HFPM trainers in order to maximize implementation quality and fidelity.

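### Observed co-rumination, the only primary outcome that is not self-report, is coded by researchers who know the allocation, for a reason that does not apply to coding

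*Protocol article*

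**What the plan says.** All points are from the protocol article.

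- **Status of the outcome.** The PTT, done at T0 and T4, is described under *Primary outcome variables*. The *Discussion* confirms it: "Self-reported risk for (early onset) depression and anxiety and self-reported and observed co-rumination will be the primary outcomes". The other primary outcomes are questionnaires completed by the girls.
- **Who codes.** *Coding process*: "A team of two coders (both PhD students) will code the data". Before that, "interactions in the PTT will be first transcribed by students of Developmental Psychology of VU Amsterdam"; the PhD students then divide the transcripts into thought units. The same section says that the video recordings are coded.
- **Who knows the allocation.** *Concealment mechanism*: "Participants and researchers are aware of allocation". *Who will be blinded*: "students, parents, school, and research staff will not be blind to treatment allocation". The reason given there is "Due to the organizational structure of the prevention program". Neither section exempts outcome coders.
- **Who delivers the programme.** *Train the trainers to deliver the program* says that sessions are given "by mindfulness-trained staff members (i.e., PI, PhD students and external staff members". The adverse-event section adds that each dyad keeps one trainer for all fourteen meetings.
- **Quality control.** A quarter of the dyads are double coded at each step, and agreement is computed separately for T0 and T4. The remaining interactions are each coded by one person.

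**The concern.** The girls cannot be blinded, so their questionnaire answers are open to expectation effects that no procedure can remove. The PTT is the one primary measure whose assessment could be separated from knowledge of the arm, and the plan gives this up without a reason that fits.

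The codes require judgement. Coders decide where one thought unit ends and the next begins, whether it concerns a problem, which response category it belongs to and what its topic is. The response scores are totals, deliberately not proportions, so a tendency to split speech more finely or more coarsely passes straight into the outcome. A coder who knows that a T4 conversation comes from a trained dyad may, without intending it, find less problem talk.

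A bias of this kind differs by arm, so a larger sample does not dilute it. If coding is completed unmasked, the only repair is to recode.

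**Working it through.** The article gives no figure for coding bias, so the main check sets its statements side by side. The arithmetic after that is an illustration.

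**Step 1: Are the coders unmasked?** The coders are PhD students on the project. Researchers are said to know the allocation, and research staff are said not to be blind. No exemption appears, so on the text they are unmasked.

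**Step 2: Does the stated reason cover coding?** The organisation of the programme explains why girls, parents, schools and trainers know the arm. Coding uses recordings and transcripts made earlier, and other students already handle the material before the coders do. The reason does not reach this step.

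**Step 3: Do coders also train?** PhD students are one of three trainer groups. *Recruitment* mentions two PhD students, and *Observations co-rumination T0 and T4* refers to both of them. Overlap between coders and trainers is therefore probable, but it is inferred.

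**Step 4: Does double coding protect?** With 160 dyads recorded at a wave, 0.25 × 160 = 40 are double coded and 160 − 40 = 120 rest on one coder. Agreement between two coders who both know the arm measures consistency; it cannot show a lean that they share.

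**Step 5: What depends on these codes?** In *Statistical methods for primary and secondary outcomes*, hypotheses 1(b), 5(b) and 6(b) use observed co-rumination, and hypotheses 8 and 9 use the observed topics and durations. Hypotheses 1, 5 and 6 also have a part (a) based on self-report.

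**Step 6: Illustration of size.**

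- From the article: 80 dyads (160 girls) per arm.
- Assumed: two-sided alpha 0.05; within-dyad ICC of the observed scores 0.2 to 0.8; a coding shift b of 0.1 or 0.2 SD between arms; no true effect; a plain comparison of arm means. The article's ICC of 0.20 is for depressive feelings, not for the PTT.
- Effective girls per arm: n = 160 / (1 + ICC).
- Standard error in SD units: SE = √(2/n).
- Rejection probability: Φ(b/SE − 1.96) + Φ(−b/SE − 1.96).

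| ICC | n | SE | b = 0.1 | b = 0.2 |
|---|---|---|---|---|
| 0.2 | 133.3 | 0.122 | 0.129 | 0.372 |
| 0.5 | 106.7 | 0.137 | 0.113 | 0.309 |
| 0.8 | 88.9 | 0.150 | 0.102 | 0.266 |

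Worked line for ICC 0.2 and b = 0.1: b/SE = 0.816, so Φ(−1.144) + Φ(−2.776) = 0.126 + 0.003 = 0.129. The nominal 5% becomes about 10-13% for a shift of 0.1 SD and about 27-37% for 0.2 SD.

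**The case against.** The strongest reply has five parts.

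1. **The trial is openly declared open label, and the full protocol or SAP may hold coding detail.** The declaration stands, but this is not a gap left to another document. The article states positively that research staff are not blind. If another document masks the coders, the two must be reconciled.
2. **The overlap of trainers and coders is not stated.** This stands. A reader might infer that each coder is judging girls she trained for 14 weeks. The text says neither that a coder trains nor that she codes her own dyads. The point does not need it, because the two blinding statements already make the coders unmasked.
3. **Transcripts alone are not enough.** This also stands. Video is coded, humour and sarcasm can depend on tone, and pauses of about 15 seconds and seconds per topic need timing. Coding from text alone would change the measurement, so the remedy must allow use of the recording.
4. **Safeguards exist.** Topic codes were fixed in advance, response categories are defined, and agreement is reported by wave. These limit individual discretion and already spread double coding over both waves. They do not address a bias shared by the coders, and there is no check by arm.
5. **The bias need not be large beside the planned effect.** A reader might infer that coding drift could match the effect sought. *Sample size calculation* does not support that: it plans on d = 1 for co-rumination, and 0.35 is only the smaller effect that oversampling is meant to detect. The shifts shown are a tenth to a fifth of d = 1, and 29% to 57% of 0.35.

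**Conclusion.** The point holds in a limited form. A primary outcome that requires judgement is segmented and coded by people stated to know the allocation, and the reason given does not cover that step. Nothing in the plan would detect a bias common to both coders.

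It should be fixed, but it does not undermine the whole trial. Hypotheses 1, 5 and 6 keep a self-report analysis, and the sample size calculation does not mention the PTT. Hypotheses 8 and 9 have no such alternative.

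The conclusion that coders are unmasked rests only on the article's own statements. The figure of 10-37% rests on the assumed shift of 0.1 to 0.2 SD, the assumed ICC range and alpha, and a simple comparison in place of the planned cross-lagged model. It shows how sensitive the test is to modest drift; it does not estimate the drift.

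**What to change.** Make these changes before coding begins:

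- At transcription, replace dyad identifier, arm and wave by a random code, remove references to the app or the training, and add time stamps for pauses and durations.
- Segment and code mainly from these masked transcripts, in random order with T0 and T4 mixed. Open the recording, under the same random code, only where tone or timing is needed, as for Humor and Silence.
- Assign no coder a dyad she trained.
- Balance the double-coded 25% by arm as well as by wave.
- Amend *Who will be blinded*, and the matching line in *Concealment mechanism*, to say that outcome coding is masked as far as possible.

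The cost is some clerical work by the students who already transcribe; no extra staff, visits or burden on the girls. Masking will be imperfect where girls mention the programme, where the recording has to be opened, or where a coder recognises a dyad from its problems. Log the cases in which the arm or the dyad became known, and run a sensitivity analysis without them.

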**Methods:**

A cluster Randomized Controlled Trial (cRCT) will be conducted to evaluate HFPM effectiveness. We will recruit 160 female friendship dyads (*n* = 320 girls) aged 13 to 15 years who will be characterized by high levels of self-reported co-rumination. The cRCT has two arms: (1) an intervention condition in which 160 girls (80 friendship dyads) will receive the 14-week HFPM program in two consecutive cohorts (cohort 1 in academic year 2023/2024 and cohort 2 in academic year 2024/2025, and (2) a control condition in which 160 girls (80 dyads) will receive care-as-usual (CAU) in two consecutive cohorts (cohort 1 in academic year 2023/2024 and cohort 2 in academic year 2024/2025). Data will be collected at baseline (T0), during the program (T1;T2; T3), immediately after the program (T4), and at 1-year follow-up (T5). Participant-level self-reported risk for (early onset) depression and anxiety, self-reported and observed co-rumination, self- and friend-reported friendship quality, self-reported positive and negative affect, self-reported interpersonal responses to positive affect, and self-reported anhedonia symptoms will be the outcome variables.

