### Timeline of the intervention and measures

The 14-week HFPM program will be delivered in two cohorts (cohort 1: academic year 2023–2024; cohort 2: academic year 2024–2025) in four phases between February 2024 and May 2025 for both cohorts. The T0 baseline measurements for both cohorts will take place from October 2023 (cohort 1) and from October 2024 (cohort 2), followed by T1 measurements (from February 2024 for cohort 1 and from December 2024 for cohort 2), T2 measurements (from April 2024 for cohort 1 and from February 2025 for cohort 2), T3 measurements (from June 2024 for cohort 1 and from April 2025 for Cohort 2), T4 post-intervention measurements (from September 2024 for cohort 1 and from July 2025 for cohort 2), and a 1-year long-term follow-up measurement (T5) from July 2025 to 2026 (see Fig. 1).

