### Statistical methods for primary and secondary outcomes

Hypothesis 1 “Girls in the intervention group will have a greater reduction in co-rumination about distress and difficult emotions and feelings, (and thereby) internalizing symptoms and negative affect during the intervention period, immediately after the intervention period and after 1-year follow-up, relative to girls in the control condition” will be tested via (a) a multi-level parallel process, dual latent growth curve model (with co-rumination measured via self-report) and (b) a multi-level autoregressive cross-lagged model (with co-rumination measured via observation [100, 101]).

For analysis (a) with co-rumination measured via self-report (T0 to 1-year follow-up T5), we will use multi-level parallel process, dual latent growth curve (LGM) models, with intervention arm as the exogenous predictor variable, growth rate of co-rumination as the mediating variable, and growth rate of internalizing symptoms and negative affect as (correlated) outcome variables. See Fig. S3 for a simplified visual representation of this model.

For analysis (b) with co-rumination measured via observations (T0 and T4), we will use a multi-level autoregressive crossed-lagged model, with intervention arm as the exogenous predictor variable (relative change from T0 to T4 in) co-rumination as the mediating variable and (relative change from T0 to T4 in) internalizing symptoms and negative affect as (correlated) outcome variables. See Fig. S4 for a simplified visual representation of this model.

Hypothesis 2 “Girls in the intervention group will have (a) a later onset of depressive symptoms or a later onset of depressive disorder and (b) less dyadic depression contagion during the intervention period, immediately after the intervention period and after 1-year follow-up, relative to girls in the control condition” will be tested using discrete-time survival analysis [102] and via actor-partner interdependence modeling [103], respectively.

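### Coder agreement on the observed primary outcome is checked before single coding starts, and no check is described while 120 of 160 dyads per wave are scored by one coder

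*Protocol article*

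**What the plan says.** The protocol article places co-rumination observed in the Problem Talk Task at T0 and T4 under Primary outcome variables, and the Discussion again counts it as primary. In the section Coding process it says: "A team of two coders (both PhD students) will code the data". On the order of work it says: "The coders will first obtain interrater reliability based on 25% of the interactions and then individually code the remaining interactions". At the end of that section, after the topic codes, it adds: "For each step, 25% of the dyads will be double coded. Interrater reliability will be computed separately for T0 and T4".

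Four other statements bear on this:

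- Coding process: the PhD students cut the transcripts into thought units, and the scores are summed counts per girl, chosen over proportions.
- Who will be blinded: research staff know the allocation. The coders, as PhD students on the study, fall in that group.
- Timeline of the intervention and measures: recordings arrive by cohort, at T0 from October 2023 and October 2024, and at T4 from September 2024 and July 2025.
- Statistical methods for primary and secondary outcomes: the observed measure enters the tests of hypotheses 1, 5, 6 and 8.

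The article does not say how the 25% is drawn, whether coding starts before cohort 2 has been recorded, or how single-coded recordings are divided between the two coders.

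**The concern.** Double coding part of a set of recordings serves two purposes: it shows that the coders agree before they work alone, and it shows that they still agree afterwards. The stated sequence serves the first. The reliability step closes, then each coder works alone, and nothing later in the section reopens the comparison within a wave.

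The scores make drift easy to acquire. They are totals of thought units, and the coders do the segmenting. A coder who comes to cut speech more finely raises the counts directly, with no denominator to absorb the change. The reported reliability would then describe the double-coded quarter and not necessarily the three quarters that carry most of the weight in the analysis. If the coders also scored different shares of each arm, part of their difference would enter the arm contrast.

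**Working it through.** **Inputs.** Dyads: 160, 80 per arm (Abstract, Methods). Waves with observation: two, T0 and T4. Share double coded: 25% (Coding process). Cohort sizes: not given; an even 80/80 split is assumed, with a range of 40 to 120 dyads in cohort 1. The plan states no figure here that could be reproduced.

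**Step 1: how much is single coded.**

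- Recordings: 160 × 2 = 320.
- Double coded: 0.25 × 160 = 40 dyads per wave, 80 recordings in all.
- Single coded: 0.75 × 160 = 120 dyads per wave, 240 recordings in all.

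**Step 2: the two statements side by side.** The earlier sentence fixes a sequence: agreement first, single coding after. The later one fixes how much is double coded ("For each step, 25% of the dyads will be double coded") and how it is reported ("Interrater reliability will be computed separately for T0 and T4"). The later one ensures that T4 is not judged on T0 agreement, and that each type of code has its own check. It places no check during or after the single coding of a wave. Read together, they leave the 120 single-coded dyads per wave without a described drift check.

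**Step 3: does cohort 2 fall outside the check?** This depends on how the 40 dyads per wave are chosen.

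- Taken in order of collection: all 40 come from cohort 1 whenever cohort 1 has at least 40 dyads, and cohort 2 has no double-coded recording.
- Drawn at random from all 160: the expected number from cohort 2 is 40 × 80/160 = 20 with an even split. It is 10 if cohort 1 has 120 dyads and 30 if it has 40. The chance of none is C(c1, 40)/C(160, 40), where c1 is the size of cohort 1. That is about 1.2 × 10⁻¹⁵ for c1 = 80 and at most about 1.3 × 10⁻⁶ over the range.

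The cohort 2 gap is therefore total under one rule and practically impossible under the other, and the article states neither.

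**Step 4: what an imbalance could do (illustration only).** Suppose the coders differ by δ SD on single-coded dyads and not at all on double-coded ones, and one coder takes share p1 of the single-coded HFPM dyads and p0 of the control dyads. The arm difference then shifts by δ × (p1 − p0) × 0.75.

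| δ (assumed) | 60% vs 40% | 70% vs 30% | 80% vs 20% |
|---|---|---|---|
| 0.3 SD | 0.3 × 0.2 × 0.75 = 0.045 | 0.3 × 0.4 × 0.75 = 0.09 | 0.3 × 0.6 × 0.75 = 0.135 |
| 0.5 SD | 0.5 × 0.2 × 0.75 = 0.075 | 0.5 × 0.4 × 0.75 = 0.15 | 0.5 × 0.6 × 0.75 = 0.225 |

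With equal shares in the two arms the shift is zero for any δ. No value of δ, p1 or p0 comes from the article.

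**The case against.** The strongest reply is that the plan already does much of what is wanted. Double coding applies to every coding step and reliability is estimated for T4 in its own right, so the wave that carries the post-intervention contrast has its own check. It would be wrong to say that later coding as a whole goes unchecked. This stands, and it narrows the point to single coding within a wave.

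A reader might infer that the double-coded quarter is the earliest quarter of the recordings and that cohort 2 is left out. The text does not support this. The word for order in that sentence governs the coders' tasks and not the choice of recordings; a random quarter double coded before the rest fits equally well.

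A reader might also infer that coders and arms are confounded, because PhD students are among the trainers and could pass on dyads they trained. The article does not say that the coders are those trainers, nor how recordings are shared out. A condensed article may leave that to a coding manual, so silence is no evidence of imbalance.

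The shifts in the table cannot be read as expected bias. They rest on assumed offsets and splits, and they ignore that the planned model works with change relative to T0, which would partly absorb a stable offset when the same coder scores both waves. Nor is the effect of 0.35 SD in the Sample size calculation a fair yardstick: that paragraph is built on depressive feelings, not on observed counts.

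None of this removes the stated order. Even a random quarter, if completed before single coding, says nothing about agreement during it.

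**Conclusion.** The point holds in a limited form. The article fixes a sequence in which agreement is established before single coding. It gives separate estimates for T0 and T4 but describes no agreement check while the remaining 120 of 160 dyads per wave are scored, one coder each, by staff who know the allocation. This follows from the stated text and the planned 160 dyads.

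Two further parts are conditional. Cohort 2 would be left without double coding only if coding followed the order of collection and cohort 1 held at least 40 dyads. An uneven split of coders over the arms is a risk that nothing in the article rules out, but it is not a stated feature. The size of any bias is unknown. This is a worthwhile improvement to the coding procedure and not a flaw that invalidates the observed outcome.

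**What to change.** Keep the 25% total and change when and how it is used:

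- Use a small part of it for initial calibration of the two coders.
- Draw the rest at random within cohort, arm and wave. With equal cohorts, the 40 dyads per wave spread over four cohort-by-arm cells give 40/4 = 10 per cell, less the calibration part. Someone other than the coders should make the draw.
- Mix these recordings through the whole coding period without marking them as double coded, and report reliability by wave and cohort.
- Assign the single-coded dyads to the two coders at random in equal numbers per arm: 120/2 = 60 per arm and wave, 30 per coder. Keep the same coder for a dyad's T0 and T4.

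The total amount of double coding stays the same provided that calibration is taken out of the 25%; extra training recordings on top would add work. The cost is an assignment list and a short addition to the coding procedure. The reported reliability may come out slightly lower than one taken only before single coding. The change needs to be made before coding is complete.
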